### Statistical analysis

#### Primary objective

Statistical analysis will be performed in R Statistical software using the clusterPower package [28] with an intention to treat approach. The primary outcome rate will be computed for each cluster and each study arm and ICCs calculated to assess cluster level variability prior to the primary analysis. The primary effectiveness measure will be compared between arms by estimating a mixed effect logistic regression model with cluster as a random intercept. The model will be adjusted for all known confounders at the individual and cluster level. There is no planned midpoint evaluation as no serious safety concerns are expected.

Apparent prevalence of HPV and STIs will be estimated in the study regions using trial data. Population prevalence of CIN2+ will be estimated based on this apparent prevalence using the reported sensitivity and specificity of the GeneXpert HPV test for this disease status (Table 5).

**Table 5 Tab5:** Diagnostic test characteristics for moderate and severe cervical lesions

	CIN2+	CIN3
Sensitivity	90.8%(84.7–95.0%)	92.3%(84.8–96.9%)
Specificity	42.6%(38.5–46.9%)	40.0%(36.1–44.0%)

Secondary outcomes compared between arms will be estimated in a similar manner. The effect of each study arm on HPV incidence is estimated using a multi-level logistic regression model as per the primary analysis. The effect of each study arm on CCS knowledge and patient experience will be estimated using a multi-level Poisson model, adjusted for the same individual and cluster level confounders with the addition of HPV status as an individual compounder and with person-time in follow-up as an offset.

Planned secondary analyses include estimating the group by arm interaction of HIV and other STI status on effectiveness of each CCS model. This will be done by adding an interaction term for each comorbidity and arm in the primary model. Temporal trends in HPV incidence and follow-up will be presented graphically.

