### Secondary objectives

Cost-effectiveness of the intervention will be estimated using a societal perspective and including all health system and out of pocket costs incurred for women participants in each arm. A decision tree model will be developed based on the patient pathway through care (See Fig. 2) in each study arm and probabilities estimated along the pathway using study data. This decision tree will inform a validated Monte Carlo simulation of HPV data and cervical cancer incidence to compare health outcomes and costs associated with each study arm. Sensitivity analysis will be performed to assess uncertainty around cost estimates, and model inputs such as HR-HPV test sensitivity and specificity and disease progression rates. The primary outcome used will be incremental cost effectiveness ratio and percent reduction in lifetime cervical cancer risk compared between the two study arms.

Process evaluation will be performed using a study specific logic model framework to define inputs, activities and outcomes (See Fig. 3.). Process evaluation was informed by the RE-AIM framework [26] and will evaluate reach, acceptability, fidelity and adoption of the screening programs from the participants and health workers perspectives. This analysis will utilize process data collected during implementation of each arm, such as study logs and checklists along with qualitative focus group data and follow-up knowledge and experience survey data.

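### With Table 5's specificity of 42.6%, the planned CIN2+ prevalence estimate is negative whenever HPV positivity is below 57.4%

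*Protocol article*

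**What the plan says.** Under Statistical analysis, Primary objective, the article sets out two linked steps. First: "Apparent prevalence of HPV and STIs will be estimated in the study regions using trial data". Then: "Population prevalence of CIN2+ will be estimated based on this apparent prevalence using the reported sensitivity and specificity of the GeneXpert HPV test", with a pointer to Table 5.

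Table 5 gives, for CIN2+, sensitivity 90.8% (84.7 to 95.0) and specificity 42.6% (38.5 to 46.9). For CIN3 it gives sensitivity 92.3% (84.8 to 96.9) and specificity 40.0% (36.1 to 44.0). The article does not say in which women these figures were measured.

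The estimate is meant for the women who are screened. Under Participants and recruitment, these are eligible women aged 25 to 49 approached in the study villages. They are not a group already selected for an abnormal result. No expected HPV positivity appears anywhere in the article, and nothing is said about an estimate that falls outside 0 to 100%.

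Under Secondary objectives, the cost-effectiveness paragraph lists "model inputs such as HR-HPV test sensitivity and specificity and disease progression rates" among the items to be varied in sensitivity analysis. It does not refer to Table 5.

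**The concern.** A specificity of 42.6% for CIN2+ means that 57.4% of women without CIN2+ test HPV positive. If that held in the study villages, well over half of the women screened would be positive even with no CIN2+ at all. The article gives no reason to expect this. The Background says that nearly all sexually active women are infected at some time and that most clear the infection within 24 months. Neither statement fixes how many are positive on one day.

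If observed positivity is lower than these inputs allow, no CIN2+ prevalence between 0 and 100% is consistent with the data and Table 5 together. The planned step would then produce either a negative prevalence or a value held at the boundary. At stake is a descriptive population figure that readers could take as the burden of precancer in the district.

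**Working it through.** **Inputs.** Se = 0.908 and Sp = 0.426 for CIN2+, Se = 0.923 and Sp = 0.400 for CIN3, with the intervals above (Table 5). AP, the observed HPV positivity, is not given, so 20% to 70% is taken as an assumed range that runs past the threshold. The article states no CIN2+ prevalence, so there is no figure to reproduce.

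**Formula.** With P the true prevalence:

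AP = Se × P + (1 − Sp) × (1 − P), so P = (AP + Sp − 1)/(Se + Sp − 1).

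This is the Rogan-Gladen correction. The article does not name it. It is inferred from the use of apparent prevalence together with sensitivity and specificity.

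**CIN2+.** Denominator: 0.908 + 0.426 − 1 = 0.334. Numerator: AP − 0.574. Hence P = (AP − 0.574)/0.334. This is zero at AP = 57.4% and reaches 100% at AP = 90.8%.

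**CIN3.** Denominator: 0.923 + 0.400 − 1 = 0.323. Hence P = (AP − 0.600)/0.323, with zero at AP = 60.0%.

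| Assumed HPV positivity | CIN2+, Sp 42.6% | CIN2+, Sp 38.5% | CIN2+, Sp 46.9% | CIN3, Sp 40.0% |
|---|---|---|---|---|
| 20% | −112% | −141.6% | −87.8% | −123.8% |
| 30% | −82% | −107.5% | −61.3% | −92.9% |
| 40% | −52% | −73.4% | −34.7% | −61.9% |
| 50% | −22% | −39.2% | −8.2% | −31.0% |
| 60% | +7.8% | −5.1% | +18.3% | 0.0% |
| 70% | +37.7% | +29.0% | +44.8% | +31.0% |

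(CIN2+ columns use Se 90.8%; the CIN3 column uses Se 92.3%.)

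**Uncertainty in Table 5.** The zero point is 1 − Sp. For CIN2+ it runs from 1 − 0.469 = 53.1% to 1 − 0.385 = 61.5%. For CIN3 it runs from 1 − 0.440 = 56.0% to 1 − 0.361 = 63.9%. Sensitivity changes the size of the estimate but not its sign, because the denominator stays positive even at both lower limits (0.847 + 0.385 − 1 = 0.232).

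**Forward check.** Table 5 implies an HPV positivity of 57.4% when CIN2+ prevalence is 0. At 2% CIN2+ it implies 0.02 × 0.908 + 0.98 × 0.574 = 58.1%. At 10% it implies 0.10 × 0.908 + 0.90 × 0.574 = 60.7%.

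**Sampling error.** The Sample size section assumes 15 clusters per arm and 70 women per cluster, so n = 2 × 15 × 70 = 2,100. At AP = 30%, ignoring clustering, SE(P) = √(0.3 × 0.7/2100)/0.334 = 0.010/0.334 = 0.030. As a rough stress test, take the largest ICC in Table 4, 0.20. It was chosen there for follow-up, so using it for HPV positivity is an assumption. The design effect is 1 + 69 × 0.20 = 14.8, and the SE becomes 0.030 × √14.8 = 0.115. An estimate of −0.82 is still about seven standard errors below zero, so chance does not account for it.

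**The case against.** Four points can be made for the plan.

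*No estimator is named.* A full analysis plan might use a truncated or Bayesian version that cannot go negative. That is fair as to form, and the formula above is an inference. But the relation between AP, Se, Sp and P holds whatever the estimator. With the Table 5 inputs and positivity below the threshold, a constrained estimate sits at or near zero and reflects the boundary rather than the data. The article fixes both the step and its inputs, so this is not a detail left to another document.

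*Positivity might exceed the threshold.* A reader might infer that the analysis is bound to return an impossible number. The article does not support that, because it gives no expected positivity. The result is inadmissible only if positivity is below about 53% to 61%. This objection stands, and the conclusion must be conditional.

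*The cost-effectiveness result.* A reader might infer that the same values would distort the ICER. The article does not show this. It never ties Table 5 or the CIN2+ estimate to the decision model, it takes pathway probabilities from study data, and it plans to vary test accuracy. Both arms use the same test and the same pathway after a positive result, so neither the direction nor the size of any effect on the incremental comparison can be stated.

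*The estimate is minor.* Population CIN2+ prevalence is neither the primary outcome nor a listed secondary outcome. In Table 2, CIN2+ appears only as detection rates over time, a fidelity measure from clinical data. This also stands, and it limits the weight of the point.

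**Conclusion.** The point holds in conditional form. With the stated inputs, no admissible CIN2+ prevalence exists below 57.4% HPV positivity (53.1% to 61.5% over the specificity interval), and none exists for CIN3 below 60.0%. This rests on Table 5 as printed and on reading the step as the usual correction from apparent to true prevalence. It does not rest on any claim about what positivity the trial will observe.

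The article offers no ground for assuming that Table 5's specificity carries over to village women aged 25 to 49. Just above the threshold the estimate is also fragile: at 60% positivity it runs from −5.1% to +18.3% over the specificity interval alone.

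The step should be corrected, but the consequence is confined to a descriptive figure. The mixed logistic comparison of VIA attendance does not use it.

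**What to change.** 1. Delete the back-calculation with the Table 5 values and report HR-HPV prevalence directly.
2. Report VIA and biopsy findings only as results among HPV-positive attenders and referred women. Under Intervention, VIA is reached only by HPV-positive women who attend, and biopsy only by those referred with suspicious lesions, so these findings cannot stand in for population CIN2+ prevalence.
3. If a population estimate is still wanted, fix in advance, on population grounds, a sensitivity and specificity from an unselected screening population, and carry their uncertainty into the interval. Do not choose the specificity after seeing the positivity.
4. Use the condition that positivity must exceed 1 minus specificity only as an admissibility check. If it fails, report that the inputs do not fit the population; do not truncate to zero.
5. Check whether Table 5 values serve as base-case inputs to the cost-effectiveness model. If they do, apply the same scrutiny there.

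Cost: items 1, 2 and 4 change one paragraph and one table and need no new data. Item 3 needs an external accuracy source that the article does not contain. Item 5 is a check of the model inputs. Design, recruitment and data collection are untouched.

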### Trial design

Advances in Screening and Prevention in Reproductive Cancers (ASPIRE) Mayuge is a pragmatic, sequential, two-arm cluster-randomized trial in Mayuge district, Eastern Uganda. The sequential nature of the study arms was chosen to prevent contamination between arms related to the enhanced community mobilization efforts included in arm 2. Ethics approval was granted from the University of British Columbia / Children’s and Women’s Health Centre of British Columbia Research Ethics Board (UBC C&W REB # H17–03332) and the Uganda Cancer Institute Research Ethics Committee (UCIREC REF-02-2018). All study participants have provided informed consent.

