### Study outcomes

Study outcomes were determined by applying RE-AIM framework [18] to intervention objectives. The primary outcome for this trial is measured at the individual level as positive or negative attendance for follow-up VIA screening (endline) at a designated Health Center after a positive HR-HPV test, among all participants screened per arm.

Secondary outcomes compared between arms include:
Cervical cancer screening knowledge measured as the count of correct responses to knowledge questions per individual within 6 months of recruitment.Patient-reported experience measures for self-collected cervical cancer screening at intervention completion at the individual level within 6 months of recruitment.HPV incidence at baseline as a sensitivity analysis to test our assumption of equal distribution of HR-HPV among the study population.

A summary of objectives, outcomes and analysis plans can be found in Table 2.

**Table 2 Tab2:** ASPIRE Mayuge Evaluation Strategy

Research Objective	Research Question	RE-AIM Outcome	Outcomes	Data Analysis Approach
Primary Objective				
Self-collected cervical cancer screening effectiveness				
To compare the effectiveness of two self-collected CCS models at improving VIA follow-up: community health worker recruitment (door-to-door) versus community health day.	Which of the two self-collected CCS models is more effective at improving VIA follow-up among screened women: door-to-door screening or community health days?	Effectiveness (Individual level)	Primary Outcome: Follow-up attendance for VIA screening at a designated Health Center after a positive HR-HPV test out of all participants screened per arm	Quantitative analysis of clinical data: Mixed effect model with cluster as a random intercept and adjusted for all known confounders. Intention to treat and sensitivity analysis; Multivariate logistic regression
	What is the: prevalence of HR-HPV types; incidence of cervical cancer; association between HPV and STIs (gonorrhea and chlamydia); and risk difference in VIA follow-up between WLWHA vs non HIV?	n/a	HR-HPV prevalence; cervical cancer incidence; STI-HPV association; HIV-HPV association; Risk difference in VIA follow-up attendance between WLWHA vs. non HIV	Quantitative analysis of clinical and survey data: Descriptive statistics: prevalence, incidence; Bi-variate analysis: adjusted odds ratio, Risk difference (adjusted for cluster and other confounders)

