	What is the effect of screening model on CCS knowledge retention and follow-up uptake? Are women aware of cervical cancer and how knowledgeable are they about CCS?	Effectiveness (Individual level)	Mean CCS knowledge scores; cervical cancer awareness;	Quantitative analysis of survey data: multi-level Poisson model;
	What are the motivators or inhibitors of CCS behaviour among women?	Effectiveness (Individual level)	Primary and secondary factors that motivate self-collected CCS; Primary and secondary factors that motivate VIA follow-up; Primary and secondary factors that inhibit VIA follow-up; Perceived social support from CHWs;	Quantitative analysis of survey data: descriptive statistics; Chi squared; multivariate logistic regression; Qualitative analysis of open-ended survey questions: deductive thematic analysis
Secondary Objectives				
Cost and feasibility				
To evaluate the cost and feasibility of a community-based CCS program in a low resource setting.	Which CCS model is more cost-effective?	Implementation (Setting level)	Cost-effectiveness of each CCS model (total provider, laboratory, transportation, equipment, training, and treatment costs per arm)	Quantitative analysis of facility survey data: ICER and reduction in CCS over lifetime; sensitivity analysis
	What are the costs associated with a CCS program?	Implementation (Setting level)	Monetary and time costs of CHWs and health care providers; training costs; laboratory costs; treatment costs; patient time costs;	Process evaluation: Narrative assessment/quantitative analysis of study logs: Descriptive statistics - univariate analysis (frequencies)
Best Practices for integrated community care				
To identify the barriers and facilitators of implementation, implementation reach, and fidelity for each model of CCS.	What are patients’ preferences for integrated service delivery? (barriers/facilitators of implementation)	n/a	Patients’ preferences for integrated service delivery	Quantitative analysis of survey data: Chi squared; multivariate logistic regression
	What is the acceptability of a community-based CCS program among participants? (barriers/facilitators of implementation)	Effectiveness (Individual level)	Patient-reported experiences with a community-based CCS program	Quantitative analysis of survey data: Descriptive statistics with time from sample collection to patient experiences survey as offset; Qualitative analysis of open-ended survey questions: deductive thematic analysis

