### Sample size

Sample size for the study was restricted to the 31 villages in the region available for randomization. Power was estimated using R statistical software across a range of plausible interclass correlation coefficients (ICCs) and absolute changes in follow-up rate from the baseline of 20% in one study arm. Power calculations assumed 15 clusters per study arm with an average size of 70 women per cluster. Power estimates were repeated using a cluster size of 50 women per village with negligible effect. Using these assumptions, we are adequately powered for a 20–30% absolute change in the outcome rate between the study arms, and up to 10% absolute change if low heterogeneity in clusters is found (see Table 4).

**Table 4 Tab4:** Power to detect difference in follow-up simulated across a range of ICCs and effect sizes

ICC	10% absolute increase in follow-up	20% absolute increase in follow-up	30% absolute increase in follow-up
0.01	98%	> 99%	> 99%
0.05	71%	> 99%	> 99%
0.10	47%	95%	> 99%
0.20	28%	75%	98%

A sup-group of women from each arm will complete a follow-up survey to assess cervical cancer screening knowledge retention and patient experience within six months of enrollment. Cluster stratified random sampling was used to select a subset of 25 participants from each cluster to total 375 participants from arm 1 and 400 from arm 2 for this survey. The survey sample size was calculated using a fixed number of clusters [23]; an ICC of 0.5; and assuming a mean knowledge score of 8 in arm 1 and 6 in arm 2 with a coefficient of variation of 1 for this score. Based on these assumptions 25 participants per cluster would result in 83% power to detect this target difference.

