### Data collection methods

Primary trial data is captured through a survey of all participants at enrollment; a follow-up survey within 6 months of results; an audit of laboratory result logs; VIA screening logs; and referral and treatment logs at the participating facilities. All enrollment surveys are administered by a trained CHW in Lusoga or English based on the language of preference of the participant. The Core Plus module 1 (CPLUS1) from the Improving Data for Decision Making in Global Cervical Cancer Programs Toolkit-Part 2 (IDCCP) [24] is used to survey eligible women at enrollment. Modifications have been made to the tool to capture participants’ socio-demographic characteristics, preferences on integrated service delivery, and issues related to HIV and other health conditions in collaboration with local partners.

After completion of CCS follow-up and within 6 months of baseline recruitment, an additional subgroup of 775 participants are recruited by a research assistant to complete a knowledge retention and patient-experience survey to better understand inhibitors and facilitators to self-collected CCS behaviour. The CCS knowledge and patient experience survey design was primarily informed by the IDCCP CPLUS1 module [24] and the Organisation for Economic Co-operation and Development’s (OECD) patient-reported experience measures (PREMs) survey tools [25]. Questions regarding knowledge and awareness were taken from Mukama et al.’s [26] survey tool which was previously used to assess CCS knowledge among women in Eastern Uganda. Additional questions were developed to capture motivations for self-collection that are specific to intervention activities.

A supplementary survey is distributed to approximately 300 men in the Mayuge district who attend the community health meetings for arm 2. The men’s survey was designed using the IDCCP CPLUS1 module [24] to capture demographic information, their level of knowledge regarding HPV and cervical cancer and how that informs their attitudes about screening for their partners. It is administered by a CHW and will be conducted in a semi-private location. All responses to the men’s survey remain anonymous and no names are collected.

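### A person-time offset is specified for a one-time knowledge score and for patient experience, so any difference between arms in survey timing would pass straight into the arm ratio

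*Protocol article*

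**What the plan says.** Under Statistical analysis (Primary objective), the article states that "The effect of each study arm on CCS knowledge and patient experience will be estimated using a multi-level Poisson model". The model is adjusted for the confounders used in the primary analysis, with the addition of "HPV status as an individual compounder and with person-time in follow-up as an offset".

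Study outcomes defines the first of these outcomes as "Cervical cancer screening knowledge measured as the count of correct responses to knowledge questions per individual within 6 months of recruitment".

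Table 2 describes the two outcomes differently. The knowledge row names a multi-level Poisson model and no offset. The row on patient-reported experience gives "Descriptive statistics with time from sample collection to patient experiences survey as offset".

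The survey is not tied to a fixed day. Data collection methods first lists "a follow-up survey within 6 months of results", then places the knowledge and experience survey "After completion of CCS follow-up and within 6 months of baseline recruitment".

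Sample size bases the survey on "a subset of 25 participants from each cluster to total 375 participants from arm 1 and 400 from arm 2", with mean scores of 8 in arm 1 and 6 in arm 2, an ICC of 0.5, a coefficient of variation of 1, and 83% power.

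**The concern.** An offset suits events that accumulate over exposure, such as infections per woman-year. A test score taken once is not of that kind: the number of questions sets its ceiling, and waiting longer creates no further opportunity to answer correctly. With log time as an offset, a woman surveyed at 6 months is expected to have twice the score of an otherwise identical woman surveyed at 3 months. Nothing in the article explains why that should be so.

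The model then compares correct answers per unit of time, whereas the survey was sized to compare mean scores. If the arms are surveyed at different average lags, the difference in lag appears as an arm effect. It could create a difference where none exists or hide a real one. Two of the three listed secondary outcomes are exposed to this.

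**Working it through.** **1. The plan's own power figure.** Inputs from Sample size: 25 women per village, 375 and 400 women (15 and 16 villages), means 8 and 6, ICC 0.5. Assumed, because not stated for the survey: two-sided 5% and a normal approximation.

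- Design effect: 1 + (25 − 1) × 0.5 = 13.
- With variance equal to the mean: SE² = 13 × (8/375 + 6/400) = 13 × 0.03633 = 0.472, so SE = 0.687.
- Power = Φ(2/0.687 − 1.96) = Φ(0.95) = 82.9%, against 83% stated.

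The figure is reproduced when the coefficient of variation of 1 is read as a variance-to-mean ratio of 1. Read literally, as an SD equal to the mean, it gives 19%. What matters here is that the calculation uses raw scores and no person-time.

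**2. What the offset does.** The model is log E[Y] = log(t) + a + b·arm, that is E[Y] = t × exp(a + b·arm). In the unadjusted Poisson fit each arm's rate is total score divided by total time. The estimated ratio (arm 2 over arm 1) is therefore

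(mean score 2 / mean score 1) × (mean time 1 / mean time 2).

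With village effects and covariates this holds approximately.

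**3. Numbers put in.** The article gives no lag by arm, so every lag below is an assumption. There is no true effect in any row. The simulation used Poisson counts with mean 7 in both arms, 15 and 16 villages of 25 women, a between-village SD of 0.15 on the log scale, exchangeable GEE and 300 runs per row.

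| Mean lag, arm 1 vs arm 2 (months) | Ratio by formula | Simulated ratio | Declared significant |
|---|---|---|---|
| 4 vs 4 | 1.00 | 0.99 | 7% |
| 4 vs 4.4 | 0.91 | 0.91 | 37% |
| 4 vs 5 | 0.80 | 0.80 | 96% |
| 3 vs 4 | 0.75 | 0.755 | 99% |
| 5 vs 4 | 1.25 | 1.25 | 93% |

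With the offset removed, the mean ratio was 0.99 to 1.01 in every timing scenario, with 5–10% declared significant.

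The last column depends on the assumed spread between villages. An SD of 0.15 implies a between-village variance of about 7² × 0.15² = 1.10 and an ICC of about 1.10/(7 + 1.10) = 0.14. At the planned ICC of 0.5 the percentages would be lower. The shift in the ratio does not depend on the ICC.

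**4. Against the planned effect.** The target ratio is 6/8 = 0.75, which is also what 3 vs 4 months produces with no effect at all. In the other direction, if arm 2's mean lag were three quarters of arm 1's, a true 6/8 would be estimated as 0.75 × (1/0.75) = 1.00.

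**5. Which time?** The statistical section counts person-time in follow-up without giving its start. Table 2 counts from sample collection. The survey window is set once from results and once from recruitment. These clocks need not agree.

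**The case against.** The strongest reply is that the bias is conditional. Both arms share the same survey rule, and no section reports survey lag by arm. A sequential design moves the arms to different calendar periods, and that alone does not change the interval from enrolment to survey. With equal mean lags the arm ratio is unshifted, as the first row of the table shows. This stands. A reader might infer from the sequential design that lags will differ and that the comparison is therefore biased, but the article supports only that they could. Results reach women by home visit in arm 1 and at a second community day in arm 2, and the survey waits for completion of follow-up at no fixed day.

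A second reply is that Table 2 names no offset for knowledge, so the offset may not be intended there. That is a fair reading of Table 2, but the statistical section applies the offset to both outcomes, so the two places conflict.

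A reader might also hold that experience items are ratings, or that knowledge must fade with time. The article does not show how experience items are scored and gives no course for knowledge over time. The point needs neither claim: it is enough that no reason is given for a score to grow in proportion to time.

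Lastly, the primary outcome is analysed with a separate logistic mixed model for which no offset is specified. That also stands, and it limits the weight of the point.

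**Conclusion.** The point holds as a fault in a stated analysis rule. A person-time offset is unsuitable for a score taken once, it does not match the raw-score basis of the survey's sample size, and the article is inconsistent about whether it applies to knowledge and from when time is counted. For patient experience, no justification is given for a rate per unit of time, and Table 2 attaches the offset to descriptive statistics, where its role is unclear.

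The possible bias equals the inverse ratio of mean lags. It is nil with equal lags, about 0.91 for 4 vs 4.4 months, and about 0.75 for 3 vs 4 months, which is as large as the planned effect. These sizes rest on a log link, on scores that do not depend on time, and on assumed lags. The article does not show that the trial's lags differ. The matter should be fixed, but it concerns secondary outcomes in a survey subsample of 775 women and leaves the primary comparison untouched.

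**What to change.** Remove the offset for both outcomes in the Statistical analysis section, and from the experience row of Table 2. Define one time origin for the survey, use it throughout the article, and enter time from that origin to the survey as an ordinary covariate in the mixed model. The data then estimate the time slope, which is no longer fixed at 1. (This covariate version was not simulated; the check above covers removal of the offset only.)

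If a denominator is wanted for knowledge, use the number of questions, for example in a binomial mixed model with a village random intercept. Choose the model for patient experience to match how its items are scored, and state that scoring.

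The cost is analysis wording. The planned offset already requires survey timing to be recorded, so no further data collection is needed. The survey's sample size was set on raw scores and needs no change on account of the offset.

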### Subgroup interventions

To describe the association between HPV and other STI, a small sub-sample of 100 participants from each arm are provided the opportunity to self-collect for chlamydia and gonorrhea testing in addition to HR-HPV testing. For those who test positive for either of the STIs, treatment is dispensed by a nurse at the Health Centre for the patient and their partner. Treatment is provided according to National guidelines in Uganda.

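### The STI-by-arm interaction is planned within the primary model, but STI status is described for at most 200 women, too few to estimate it usefully

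*Protocol article*

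**What the plan says.** The statistical analysis section, under the primary objective, states: "Planned secondary analyses include estimating the group by arm interaction of HIV and other STI status on effectiveness of each CCS model". The method given is "adding an interaction term for each comorbidity and arm in the primary model". The primary model is a mixed-effect logistic regression with a random intercept for village and adjustment for known confounders. Under Study outcomes, its outcome is attendance at VIA follow-up after a positive HR-HPV test, assessed "among all participants screened per arm".

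Under Subgroup interventions, "a small sub-sample of 100 participants from each arm are provided the opportunity to self-collect for chlamydia and gonorrhea testing". The purpose given there is "To describe the association between HPV and other STI". Table 2 likewise lists an STI–HPV association and no arm-by-STI comparison.

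The data collection section says the enrolment survey given to every participant was modified to cover HIV and further health topics. It does not name STI status, and no other section gives a source of STI status for the untested women.

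**The concern.** The interaction is specified on all screened women, while the covariate it needs is described for a small sub-sample recruited for something else. Fitted as written with standard software, the model would keep only tested women.

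Three things are at stake:

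- The STI-by-arm estimate would be too imprecise to inform anyone, yet a non-significant result could be read as showing that the two screening models compare equally in women with and without STIs.
- The article does not say whether the HIV and STI terms share one model. If they do, missing STI results would also cut the HIV interaction down to the sub-sample, although HIV data appear to be sought from everyone.
- The article does not say how untested women are handled. Coding them as negative would misclassify an unknown number.

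**Working it through.** **The plan's own figures.** "Power calculations assumed 15 clusters per study arm with an average size of 70 women per cluster", with baseline follow-up of 20%. Taking effective n per arm = 15 × 70 / (1 + 69 × ICC) and two-sided alpha of 0.05 (assumed, as none is stated), a two-proportion calculation gives 98.3, 71.0, 46.9 and 27.8% for a 10-point increase at ICC 0.01, 0.05, 0.10 and 0.20. Table 4 prints 98, 71, 47 and 28%. All 12 cells agree within 2 points. The table concerns the main arm comparison only; no power is stated for any interaction.

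**Share of women with STI status.** At most 2 × 100 = 200, an upper bound because testing is offered. The article does not state a total number of women, so it is derived from the 31 villages, or the 15 per arm used for power, and the two village sizes considered ("Power estimates were repeated using a cluster size of 50 women per village with negligible effect"):

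| Basis | Women | Without STI result |
|---|---|---|
| 31 × 70 | 2,170 | 1 − 200/2,170 = 90.8% |
| 30 × 70 | 2,100 | 90.5% |
| 31 × 50 | 1,550 | 87.1% |
| 30 × 50 | 1,500 | 86.7% |

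Spread evenly, the 200 women are about 6 or 7 per village (200/31 = 6.5), in a model with a village random intercept.

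**Precision.** For the four arm-by-STI cells, ignoring clustering, SE of the log interaction odds ratio = √Σ[1/(n·p·(1 − p))]. The ratio detectable with 80% power is exp(2.8 × SE). The article gives no STI prevalence, so 5–20% is assumed. Outcome rates run from 4% to 30%. The low end reflects that a woman must be HR-HPV positive and attend to count among all screened; the upper values use the 20% baseline in the article and a 10-point increase.

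Example with 10% prevalence and outcomes of 20% and 30%: 1/(10 × 0.16) + 1/(90 × 0.16) + 1/(10 × 0.21) + 1/(90 × 0.21) = 0.625 + 0.069 + 0.476 + 0.053 = 1.224. SE = 1.11 and the detectable ratio is about 22.

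| Outcome, arms 1 / 2 | STI prevalence | SE | Detectable ratio |
|---|---|---|---|
| 4% / 4% | 5% | 3.31 | not meaningful (5 × 0.04 = 0.2 expected events per arm in STI-positive women) |
| 12% / 12% | 15% | 1.22 | about 30 |
| 20% / 20% | 10% | 1.18 | about 27 |
| 20% / 20% | 15% | 0.99 | about 16 |
| 20% / 30% | 5% | 1.52 | about 71 |
| 20% / 30% | 10% | 1.11 | about 22 |
| 20% / 30% | 20% | 0.83 | about 10 |

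In the last three rows, power to detect an interaction odds ratio of 3 is 11, 17 and 26%. For comparison, if all 1,085 women per arm had STI results, the detectable ratios in those rows would be about 3.7, 2.6 and 2.0.

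**Estimability.** Simulated chance that some arm-by-STI cell has no attenders or only attenders, with 100 women per arm and no clustering:

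| Outcome, arms 1 / 2 | 5% STI | 10% STI | 20% STI |
|---|---|---|---|
| 20% / 30% | 53% | 18% | 2% |
| 6% / 12% | 89% | 69% | 37% |

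The term is therefore sometimes inestimable and otherwise very imprecise.

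**The case against.** The interaction is listed as a secondary analysis, so the primary analysis loses no one. A reader might infer that the trial's main result would rest on 9% of its women; the article does not support that.

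A reader might also infer that the term cannot be estimated at all. That too goes beyond the evidence: at 20% STI prevalence and outcomes of 20% and 30%, separation is rare (2%). It becomes common only when STI is uncommon or the outcome is rare, and neither is fixed by the article.

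The denominator is derived, the prevalences are assumptions, and the Wald standard error is unreliable at the smallest expected counts. The questionnaire is not shown, so a self-reported STI item cannot be fully excluded. The article does not say how the 100 women per arm are selected, so calling them unrepresentative is unsupported; they are only not shown to be representative. Nor does it say that untested women will be coded as negative. A condensed article may leave the handling of untested women to an analysis plan.

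All of this limits the claim. It does not remove the mismatch: the article itself names the model and its population, and the STI data it describes cover only a small part of that population. The imprecision also persists at the article's own 20% rate.

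**Conclusion.** The point holds as a mismatch between a stated secondary analysis and the data described for it. A complete-case fit would discard about 87–91% of women. The interaction could not be estimated with useful precision: the detectable odds ratio is about 10 in the most favourable scenario worked (20% STI prevalence, outcomes of 20% and 30%), about 16 to 71 in the other scenarios using the article's 20% rate, and larger still as the outcome becomes rarer. Clustering and covariate adjustment are not included in these figures.

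The conclusion rests on the assumed STI prevalence, on derived totals, and on there being no STI self-report item for all women. It does not touch the primary comparison. It extends to the HIV interaction only if both terms are fitted together, which the article leaves open. A ban on every arm-by-STI summary would go further than the evidence requires; a separate, clearly exploratory one is acceptable.

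**What to change.** Amend the sentence on interactions in the statistical analysis section:

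- Keep the HIV-by-arm interaction in the primary model, fitted on all women with HIV data, and remove the STI-by-arm term from that model.
- Use the chlamydia and gonorrhoea sub-sample for its stated purpose: an estimate of the HPV–STI association, adjusted for cluster, with a confidence interval.
- If an arm-by-STI result is still wanted, fit it separately in tested women only, label it exploratory, do not code untested women as negative, and state that a null result will not be read as equal effectiveness.
- If the survey does collect STI status from all women, say so and name that variable as the one used.

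The cost is a few lines of text and no new data. A subgroup test that could not have been informative is given up or demoted.
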